### Missing data

The main analysis will be a complete case analysis. If outcome measures have missing values at follow-up or at baseline the participants will be excluded from the analysis. A range of sensitivity analyses will be conducted to assess the robustness of the findings to missing data, these will include multiple imputation and analyses assuming no change in the primary outcome compared with the baseline value in families lost to follow-up [30].

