### Analysis

Baseline characteristics will be described for the three treatment arms using frequencies and percentages for categorical variables and with means and standard deviations for continuous variables if normally distributed or, if not, with medians and interquartile ranges.

All analyses of primary and secondary outcomes will be conducted on an intention-to-treat basis in that families and children’s centres will be analysed in the group to which they were randomised, regardless of whether they received or delivered the intervention. Analyses will be undertaken blind to treatment arm allocation. Statistical significance will be assessed based on likelihood ratio tests with a p value of <0.05 taken as significant. Analyses will be undertaken using Stata.

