### Primary outcome measure

The proportion of families who report that they have a fire escape plan will be compared between treatment arms (IPB plus facilitation versus control and IPB only versus control) using random effects logistic regression to estimate odds ratios and 95% CI. The model will include randomisation stratum (trial site: Nottingham, Bristol, Norwich, Newcastle) as a fixed effect and will adjust for three cluster level variables (lead agency of the children’s centre (Local Authority, NHS or Voluntary sector led), Ofsted report scores for overall effectiveness and capacity for sustained improvement [29]) and two family level variables (having a fire escape plan at baseline and the Index of Multiple Deprivation (IMD) 2010 score [14]). These variables were selected as they are considered likely to be strongly associated with the outcome variable. The main comparisons will be between the IPB plus facilitation group versus control and the IPB only group versus control; a significance level of 0.05 will be used for each of these comparisons. Sub-group analyses will explore differential effects of the interventions by IMD, by adding interaction terms to the regression model. The intraclass correlation coefficient with a 95% CI will be estimated from the random effects regression model.

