### Secondary outcome measures

#### Family level outcome measures

Binary secondary outcomes will be compared between treatment arms (IPB plus facilitation versus control and IPB only versus control) using random effects logistic regression and ordinal outcomes will be compared using random effects ordinal regression. Continuous outcomes will be compared using random effects linear regression, where assumptions are met. Where assumptions are not met, we will examine the distribution of the continuous outcome measure and categorise appropriately and analyse with ordinal or logistic models. Models will include randomisation stratum as a fixed effect and will also adjust for three cluster level variables (the lead agency of the children’s centre (Local Authority, NHS or Voluntary sector led [29]), and Ofsted report scores for overall effectiveness and capacity for sustained improvement) and two family level variables (baseline value of the secondary outcome measure, IMD).

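### The main analysis avoidably drops families with an observed 12-month outcome when only the baseline value of that outcome is blank (minor)

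*Protocol article*

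**What the plan says.** Under Missing data, the protocol article states "The main analysis will be a complete case analysis" and then: "If outcome measures have missing values at follow-up or at baseline the participants will be excluded from the analysis". The sensitivity analyses follow: "these will include multiple imputation and analyses assuming no change in the primary outcome compared with the baseline value in families lost to follow-up".

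Baseline values matter because the models adjust for them. The primary model (Primary outcome measure) includes "two family level variables (having a fire escape plan at baseline and the Index of Multiple Deprivation (IMD) 2010 score". The family-level secondary models (Family level outcome measures) include "baseline value of the secondary outcome measure, IMD".

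The Analysis section says: "All analyses of primary and secondary outcomes will be conducted on an intention-to-treat basis". It explains this to mean that families and centres "will be analysed in the group to which they were randomised, regardless of whether they received or delivered the intervention".

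Two further points set the scope. Under Families, a family counts as recruited only once it has returned a consent form and a completed baseline questionnaire. Under Randomisation, a centre is randomised only after 30 families have been recruited there.

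**The concern.** The rule treats a blank baseline item like a missing outcome. The two differ. Without the 12-month outcome, a family contributes no direct information on the effect. With the outcome but no baseline value, it contributes almost all of it and lacks only a covariate that sharpens the estimate.

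Three things are at stake:

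- **Precision.** Outcome data already collected are discarded.
- **A shifting analysis set.** Each secondary outcome with a baseline value is adjusted for its own baseline, so the families analysed change from one outcome to the next.
- **Who is represented.** The Discussion says that families in these areas may have lower literacy. If those families skip more items, the analysed set moves away from the families the trial is aimed at. This is plausible, but the protocol does not show it.

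**Working it through.** **1. When the baseline value is collected.** Recruitment requires the baseline questionnaire, and randomisation of the centre follows recruitment of its 30 families. Baseline values, and gaps in them, therefore precede allocation. Arm cannot cause the gaps, and dropping these families amounts to restricting the analysis by a pre-randomisation characteristic. No recruited family lacks the whole questionnaire, so only blank items can trigger the rule.

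**2. The protocol's own sample size.** Inputs from Sample size: 42% v 62%, ICC 0.05, 20 families analysed per centre, 80% power, two-sided 5%.

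- Design effect: 1 + (20 − 1) × 0.05 = 1.95.
- Families per arm under individual randomisation, with continuity correction: 107. Then 107 × 1.95 = 208.65, and 208.65 / 20 = 10.43, so 11 centres, as stated. Without the correction: 97 × 1.95 / 20 = 9.46, so 10 centres.
- Families recruited per centre: 20 / (1 − 0.33) = 29.9, so 30; and 36 × 30 = 1080, as stated.
- The 33% allowance is labelled loss to follow-up and is used up in reaching 20 per centre (30 × 0.67 = 20.1). Nothing is set aside for blank baseline items.

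**3. What the rule costs on the primary outcome.** The protocol gives no rate of blank baseline items, so let q be the assumed share of followed-up families lacking the baseline item. With k centres per arm:

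- m = 20(1 − q)
- design effect D = 1 + (m − 1) × 0.05
- SE = √{[0.42 × 0.58 + 0.62 × 0.38] × D / (k × m)} = √{0.4792 × D / (k × m)}
- power from a noncentral t distribution with 2k − 2 degrees of freedom and noncentrality 0.20 / SE.

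For k = 11 and q = 0: SE = √(0.4792 × 1.95 / 220) = 0.0652, noncentrality 3.07, 20 degrees of freedom, power 83.1%.

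| q (assumed) | Families lost of 660 (11 per arm) | Power, 11 centres per arm | Power, 12 centres per arm |
|---|---|---|---|
| 0 | 0 | 83.1% | 86.5% |
| 3% | 20 | 82.6% | 86.0% |
| 10% | 66 | 81.1% | 84.7% |
| 15% | 99 | 80.0% | 83.6% |

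Twelve per arm is the number to be recruited (36 / 3). A normal approximation gives the same gentle decline: 85.7% to 83.9% between q = 0 and 10% at 11 centres, or 82.4% to 80.2% with continuity correction. The loss is small because, with clustering, removing a few families per centre also lowers the design effect (1.95 to 1.85 at q = 10%).

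**4. Composite secondary outcomes.** The fire escape planning measure is derived from five items. If each item is independently blank for 1-3% of families, and any blank makes the measure missing (both assumptions), the share without a baseline value is 1 − 0.99⁵ = 4.9% to 1 − 0.97⁵ = 14.1%. The bedtime routine score and the knowledge count may be similarly exposed.

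**The case against.** **Adjustment explains the rule.** A complete case analysis of a model with a baseline covariate drops records lacking that covariate. This stands as an explanation, so the rule is not arbitrary. It does not make the rule necessary, since the model can be fitted with those families kept.

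**Intention-to-treat.** A reader might infer that the rule breaks the stated intention-to-treat analysis. The documents do not support that. The Analysis section defines the term by allocated group, regardless of receipt or delivery, and says nothing there about missing data. Complete cases analysed by allocated arm are consistent with it.

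**Bias.** A reader might also infer that the arm comparison is biased. Because the gaps arise before allocation, the exclusion does not itself create imbalance between arms. It can change which families the estimate describes.

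**Multiple imputation is already planned.** True, but only as a sensitivity analysis, so the headline estimate still rests on the reduced set. The other analysis named, no change from baseline in families lost to follow-up, does not deal with blank baseline values.

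**Scope.** It would be too much to say that every secondary outcome is affected. Ascertaining family outcomes adds resource use and services attended, such as smoking cessation, at the post-intervention questionnaire, so those outcomes may have no baseline value. The centre-level models listed do not adjust for one.

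**The remedy has a cost.** Odds ratios are non-collapsible, so a missing indicator does not target exactly the same adjusted odds ratio. Take 42% v 62%, baseline prevalence 42%, a single-level model and 10-20% of baseline values missing completely at random (the last three are assumptions). If the baseline-outcome odds ratio is 10, the adjusted treatment odds ratio of 2.95 becomes 2.84-2.75. If it is 4, 2.48 becomes 2.45-2.43. The unadjusted value is (0.62/0.38)/(0.42/0.58) = 2.25. This stands as a small downside, and it does not make deletion preferable.

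**Conclusion.** The point holds as a minor one. The rule excludes families with an observed outcome when a pre-randomisation covariate is blank, and this can be avoided. The harm is limited to lost precision and a set of families that varies by outcome.

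Its size rests on an assumed rate of item non-response. At 3-10%, the primary outcome loses about 0.5 to 2 percentage points of power (83.1% to 82.6-81.1% at 11 centres per arm; 86.5% to 86.0-84.7% at 12), and power stays above the 80% target. These figures use the protocol's planning values and ignore any gain from covariate adjustment. Larger losses on composite secondary outcomes are possible but cannot be established from the protocol. The case for change rests on how cheap the remedy is, since the power loss is small.

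**What to change.** Amend the Missing data section so that, in the main analysis, a family is excluded only if the 12-month value of the outcome is missing. Keep families with a blank baseline value by adding a missing indicator for that covariate, or by simple imputation of it, and name the chosen method before the data are analysed. Keep multiple imputation as a sensitivity analysis, together with the complete case analysis if wanted. Add a sentence on how the intention-to-treat statement applies to families with missing data.

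The cost is a sentence or two of text and, with the indicator method, one extra variable per affected model. No further data collection is needed. The adjusted odds ratio shifts slightly towards the unadjusted one because of the families whose baseline value is missing, and this should be acknowledged when the result is reported.

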### Health economic analysis

Cost-effectiveness will be determined by comparing cost differences between treatment arms with differences in the number of families in each group with a fire escape plan. This will be assessed by combining resource-use data collected throughout the trial with unit cost information and summed to obtain an average cost per person (together with its uncertainty) for each intervention. Secondly, these cost data will be combined with the clinical effectiveness data (eg., proportion of families who have a fire escape plan) to inform the incremental cost-effectiveness analysis. A sensitivity analysis will be undertaken to assess the robustness of the results to any assumptions made in the analysis.

### Qualitative analysis

Data from the telephone and face-to-face facilitation contacts between children’s centres and researchers will be analysed manually using content analysis after categorisation into main sub-headings [31]. A thematic analysis will then be conducted. Data from the 12 month implementation fidelity interviews will be managed using a qualitative data management package e.g. QSR NVIVO and analysed using Framework Analysis [32]. This is a structured method of qualitative data analysis where a priori themes are identified but emergent themes can also be identified and incorporated into the analytic framework. These themes will be agreed by researchers from the four trial sites and lay research advisors through an initial analysis of eight interviews, selected to represent a range of children’s centres. This framework will be used to undertake the analysis of the rest of the interviews, with further adaptation if required.

### Risks

We do not anticipate that participants will be exposed to any excess risk as a result of participating in this trial.

### Ethical and organisational review

The trial protocol was approved by the Derbyshire Research Ethics Committee (11/EM/0011) and the University of the West of England Bristol Research Ethics Committee (HSC/11/06/61). The trial received NHS organisational approval from Primary Care Trusts (PCTs) where staff who work in Children’s centres are employed by PCTs. Approval was provided by the following PCTs: Nottingham CityCare Partnership, Nottinghamshire Healthcare Trust (formerly NHS Nottinghamshire County), Bassetlaw PCT, NHS Bristol, North Somerset PCT, South Gloucestershire PCT, Norfolk PCT, Great Yarmouth & Waveney PCT, Northumbria Healthcare Foundation NHS Trust, Northumberland Healthcare Trust.

## Discussion

This trial will enable an evaluation of the effectiveness and cost-effectiveness of implementing an IPB in children’s centres for promoting fire prevention. It will also explore and assess the process of implementing the IPB using a range of methodologies, including a nested qualitative study. The intervention we have developed and are testing within this trial is a complex intervention [15] and one that children’s centres can tailor to suit their individual circumstances. Substantial preparatory work has been undertaken as part of the development of the intervention, including a review of implementing health promotion interventions to identify appropriate theoretical models, interviews with key informants and workshops with stakeholders including children’s centre managers and staff, the Fire and Rescue Service, NHS staff and commissioners of children’s services. In addition, a series of systematic reviews updating the evidence on what works in injury prevention and identifying barriers and facilitators to home injury prevention as well as surveys and interviews with children’s centre managers and staff and with parents of pre-school children to identify barriers and facilitators to injury prevention have been undertaken and their findings incorporated into the design of the trial. Our evaluation includes multiple methods to quantify and explore implementation and a range of outcome measures covering family and children’s centres outcomes, including economic outcomes.

As there is a steep social gradient in fire-related thermal injuries we considered it important to test the effectiveness of our intervention in children’s centres situated in the more disadvantaged areas in each trial site. However, families attending children’s centres in these areas may have lower levels of literacy and families with young children are likely to be more mobile than other families [33]. This may pose challenges for trial recruitment and retention, so we are using a range of recruitment and follow-up methods including small monetary incentives.

This trial will be the first randomised controlled trial to provide data on the effectiveness of implementing an IPB in children’s centres to promote fire prevention in disadvantaged populations. Findings should enhance the evidence base for fire prevention for young children. This information will be relevant for policy makers, commissioners of injury prevention services, Fire and Rescue Services, children’s centre staff and other injury prevention practitioners.
